**11. ADDITIONAL INTERVENTIONS – CHEMOTHERAPY, SURGERY AND/OR ADDITIONAL RADIATION**

11.1 Interventions prior to protocol therapy: If chemotherapy, surgery and/or radiation are recommended by the treating physicians based on the patient’s clinical needs, they may be performed two weeks before or after days 1-28 of protocol therapy.

For instance, a patient with a history of breast cancer status post mastectomy (three years ago) and adjuvant chemotherapy now presents with a solitary brain metastasis, a single lung lesion and two bone lesions. The brain metastasis and lung lesion are both amenable to resection. Subsequently, the patient receives whole brain radiation and taxane based chemotherapy. After chemotherapy, CT of the chest abdomen and pelvis and MRI of the brain reveal no evidence of metastatic disease but bone scan demonstrates residual uptake in the two bone lesions. Two weeks after completion of chemotherapy, the patient is eligible for protocol therapy. The patient will receive Sutent on days 1-28 and extracranial stereotactic radiation on days 8-12 and 15-19 as per protocol. Two weeks after protocol therapy (day 43), the patient may receive additional chemotherapy. After completion of all planned chemotherapy, the patient will start maintenance Sutent. Therefore, all of the chemotherapy, surgery and whole brain radiation are allowed by protocol but are not considered “on protocol therapy”. While all toxicities of these interventions will be documented and recorded, any toxicity resulting from non-protocol therapy will not count as dose-limiting toxicity.

11.2 If patients have documented progression during additional chemotherapy and/or maintenance Sutent, the patient will be taken off protocol. At that time, any necessary intervention (chemotherapy, surgery and/or radiation will be allowed).

**12. TOXICITY**

- Radiation side effects are limited to the area involved in the treatment field(s). Acute and late toxicity related to radiation therapy include fatigue, nausea and vomiting, myelosuppression, skin erythema, subcutaneous fibrosis, esophagitis, pericarditis, diarrhea, cystitis, proctitis, myelitis, acute radiation pneumonitis, late pulmonary fibrosis, esophageal stricture, liver dysfunction, kidney damage, small bowel obstruction.
- Sutent toxicities are discussed in detail in Section 9.7
- Grade 3-5 non-hematological toxicities (excluding nausea, vomiting, and alopecia) and Grade 4-5 hematological toxicities will be referred to as dose limiting toxicities (DLT).
  - Esophagitis and mucositis are very common side effects with radiation therapy and grade 3 side effects can be seen after palliative courses of radiotherapy. Therefore, grade 3 mucositis or esophagitis lasting ≤ 7 days will not be considered a DLT. If the grade 3 mucositis or esophagitis lasts > 7 days, it will then be considered a DLT.
- All life-threatening Grade 4 and all fatal toxicities (Grade 5) must be reported immediately and evaluated.
- Acute toxicity: Acute side effects are considered as occurring ≤ 30 days from the start of radiation therapy. They will be documented using the NCI Common Terminology Criteria for Adverse Events (CTCAE) version 3.0 (A copy can be downloaded from [http://ctep.info.nih.gov](http://ctep.info.nih.gov/)).
- Late toxicity: Late side effects are considered occurring > 30 days from the start of radiation therapy. They will be evaluated and graded according to the RTOG Late Morbidity Scoring Scale (See Appendix).

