11. Radiation is to be delivered to each site over 10 fractions separated by at least 16 hours. Up to 5 sites may be treated. **(Added 7/27/06)** For patients with 3 to 5 sites of disease, it may be difficult to treat all sites of disease during one day. For these patients, an acceptable variant is to treat all 2 to 3 sites during days 8 to 19 and to treat the remaining sites on days 20 to 33. For these patients only, concurrent Sutent will continue until day 42.
12. Radiation Doses (Phase I): A phase I escalation of doses will be performed in order to determine in MTD in Gy

Doses of radiation will increase as follows in order to determine the MTD of radiation in combination with Sutent:

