9.3 Phase I and II Maintenance dose: will be 50 mg PO QD

9.4 Schedule:

- One days 1-28, Sutent will be taken p.o. in the morning
- Two weeks after completion of any chemotherapy, maintenance Sutent in 6 week cycles (consisting of Sutent 50 mg PO QD weeks 1-4 followed by no treatment weeks 5-6) until progression or death

9.5 Formulation and Packaging: SU011248 is a small molecule inhibitor of the receptor tyrosine kinases VEGFR, PDGFR, KIT, and FLT3. In this clinical trial, study medication of SU011248 refers to the investigational agent SU011248 L-malate. Sunitinib L-malate salt will be supplied as hard gelatin capsules containing 12.5-mg, 25-mg, and 50-mg equivalents of Sunitinib malate free base, in bottles containing 30 capsules each."

9.6 Storage:Store at 25º C (*77º F*); excursions permitted to 15-30º C (*59-86º F*).

9.7 Adverse Effects: Data regarding the safety of Sutent are largely from a Phase III randomized trial of 304 patients with metastatic GI stromal tumors following imatinib failure who were treated with Sutent vs. placebo and 169 patients with metastatic renal cell carcinoma treated on phase II trails (32, 33).

Cardiac: Left Ventricular Dysfunction – The incidence of decreased left ventricular ejection fraction to below the lower limit of normal is 11-15% with Sutent vs. 3% for placebo. Over 40% of patients recover left ventricular ejection fraction without intervention. Only 1% of patients suffered grade 3 left ventricular systolic toxicity. Sutent should be discontinued in the presence of clinical congestive heart failure. The Sutent dose should be reduced in all patients without clinical congestive heart failure but with an ejection fraction of <50% and a drop of over 20% from baseline.

Hemorrhagic Events: Bleeding occurred in 18 to 26% of patients receiving Sutent vs. 17% for placebo with epistaxis being the most common hemorrhagic event. The incidence of Grade 3-4 bleeding is 1 to 7% among patients receiving Sutent vs. 9% for placebo. However, fatal pulmonary hemorrhage was noted in two patients with non-small cell lung cancer. Bleeding events, including fatal GI bleeding, has been noted in patients within 30 days of completing Sutent. Although there is no specific contraindication for concurrent anticoagulants, patients requiring continued Coumadin, lovenox, heparin, NSAIDs, aspirin, plavix or similar drugs will be excluded from this study (12/16/09).

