9.10 Dose Modifications for Sutent(Applies only to phase II)

Dose modification of Sutent can be secondary to any grade 3 toxicity related to Sutent according to the judgment of the treating physician. When toxicities eliciting dose modification occur, Sutent will be temporarily discontinued but restarted at the next lower dose level when the toxicity has resolved to grade 2 or lower. In the event of hospitalization for reasons other than drug toxicity, patients should be directed to continue trial drug at the discretion of their physician. The principal investigator should be notified immediately of any compliance issues that arise in the course of the trial. If a patient still experiences dose-modifying toxicities despite drug holiday and reduced dose schedule, the patient, if benefiting from treatment, should stop receiving Sutent and continue radiation.

The following toxicities, in addition to any other toxicity as judged by the treating physician, merit temporary discontinuation should be considered dose-limiting toxicity:

1. Any CTC grade 3 or 4 non-hematopoietic adverse event that the investigator considers consistent with a drug-related toxicity;

2. Any CTC grade 4 hematopoietic adverse event that the investigator considers consistent with a drug-related toxicity;

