  - All patients who have met the eligibility criteria will be included in the main analysis of the response rate. Patients in response categories 4 – 8 will be considered as failing to respond to treatment (disease progression).
  - All individual lesions will also be recorded as CR, PR, SD, or PD.
  - Overall survival is the time from the date of first study treatment until death from any cause.

Overall survival and progression-free survival (PFS) will be calculated using the Kaplan-Meier (1958) estimator.(40) Median survival times and their associated 90% confidence intervals will be derived using the method described in Brookmeyer and Crowley (1982).(41)

The percentage of patients with complete responses and the percentage with complete or partial responses will be calculated and confidence intervals derived. The pattern of failures (local or distant) will be summarized. Adverse effects will also be tabulated by type and level of severity. Potential prognostic variables, such as number of lesion sites at baseline, will be examined by fitting Cox (1972) regression models for progression-free and overall survival times.(42) Given the sample size, only univariate analysis will be performed.

- Accrual Rate and Study Duration
  - The estimated accrual will depend on toxicity encountered, but we anticipate enrolling 50-65 patients.
  - We anticipate enrolling 1-3 patients per month.

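### Section 12 switches the toxicity grading scale by time alone, so read literally all maintenance Sutent toxicity goes on a late-radiation scale while other rules still use CTC grades

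*Protocol*

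**What the plan says.** Section 12 (Toxicity) deals with radiation and Sutent in one list. It defines two periods by the calendar. First: "Acute side effects are considered as occurring ≤ 30 days from the start of radiation therapy", documented with CTCAE version 3.0. Then: "Late side effects are considered occurring > 30 days from the start of radiation therapy". For this second period the instruction is: "They will be evaluated and graded according to the RTOG Late Morbidity Scoring Scale (See Appendix". Neither sentence depends on the cause of the event, and neither makes an exception for drug effects.

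The list opens with radiation ("Acute and late toxicity related to radiation therapy include fatigue, nausea and vomiting, myelosuppression") and refers the reader to Section 9.7 for Sutent toxicity. Section 9.7 names no grading scale.

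Sutent continues well past the switch. Section 9.3 says: "Phase I and II Maintenance dose: will be 50 mg PO QD". The synopsis treatment plan starts maintenance on day 43 if no chemotherapy is planned, otherwise two weeks after chemotherapy ends, and continues it to progression or death. For patients with 3 to 5 sites, Section 8.1 allows a variant: "treat the remaining sites on days 20 to 33. For these patients only, concurrent Sutent will continue until day 42".

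Other rules are written in CTC or CTCAE grades and carry no 30-day limit:
- Section 6 applies CTCAE grades 3 and 4 to laboratory values at withdrawal, whenever that occurs.
- Section 9.10, headed as phase II only, lists "Any CTC grade 3 or 4 non-hematopoietic adverse event that the investigator considers consistent with a drug-related toxicity".
- The note under the reporting tables in Appendix 3 asks for a report of any hospitalizing event equivalent to CTC grade 3 to 5.

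Section 16 promises a summary: "Adverse effects will also be tabulated by type and level of severity". It does not name the scale.

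**The concern.** A scale for late radiation morbidity is assigned to a period in which the patient is taking a systemic drug and radiation has ended. The risks that Section 9.7 describes for Sutent, such as hypertension, falling ejection fraction, bleeding, and gastrointestinal and skin effects, are drug effects that can arise at any time during dosing. If Section 12 is followed as written, those events receive a grade on one scale while the rules in Sections 6 and 9.10 and Appendix 3 ask for a grade on another.

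Two things are at stake. Site staff have conflicting instructions on how to grade the same event. And the severity table in Section 16 would rest on two scales, divided at about day 38, with nothing in the protocol to match the grades of one to those of the other.

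**Working it through.** **When the scale switches.** Radiation starts on day 8 (synopsis, treatment plan). Day 8 + 30 = day 38, or day 37 if day 8 counts as the first day.

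**Where maintenance falls.** Earliest start is day 43. 43 − 38 = 5 days after the switch (6 on the other count). Every maintenance day is therefore in the RTOG period.

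**The variant for 3 to 5 sites.** Radiation to the remaining sites may run to day 33, and concurrent Sutent to day 42. Events from day 39 are late by definition.
- 39 − 33 = 6 days after the last fraction, so a radiation reaction six days after treatment counts as late.
- Concurrent Sutent on days 39 to 42 also falls in the RTOG period.
- If the clock restarted for the second group of sites, the switch would move to 20 + 30 = day 50. The text does not say that it restarts.

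**Share of Sutent dosing after the switch.** The protocol gives no figure, so this is an illustration. Assumptions: standard schedule, no chemotherapy, no missed doses or holds, registration at about day 1, 30.44 days per month. The concurrent phase has 28 dosing days, all before the switch. Maintenance runs in 42-day cycles with 28 days on drug. The times to progression are those in Section 16.

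| Progression | Day | Maintenance days | On drug after switch | Share |
|---|---|---|---|---|
| 2.2 months | 2.2 × 30.44 ≈ 67 | 43–67 = 25 | 25 | 25/(25 + 28) = 47% |
| 6.4 months | 6.4 × 30.44 ≈ 195 | 43–195 = 153 = 3 × 42 + 27 | 3 × 28 + 27 = 111 | 111/(111 + 28) = 80% |
| 10.6 months | 10.6 × 30.44 ≈ 323 | 43–323 = 281 = 6 × 42 + 29 | 6 × 28 + 28 = 196 | 196/(196 + 28) = 88% |

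If chemotherapy continues until progression, maintenance never starts and the share is 0%.

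**What does not depend on the switch.** Section 16 limits dose-limiting toxicity for escalation to 30 days from the start of radiation, which is the CTCAE period. Section 15.1 defines serious adverse events for the supporting company by seriousness, not grade.

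**The appendix reference.** The table of contents lists four appendices: consent form, performance status scales, monitoring plan, and blood and urine procedures. None is the RTOG scale to which Section 12 points.

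**The case against.** The best defence is that the late-toxicity sentence concerns radiation effects only. Section 12 opens with radiation side effects, introduces acute and late toxicity as radiation-related, times both periods from the start of radiation, and sends Sutent toxicity elsewhere. On that reading no drug event moves to the RTOG scale.

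The reading is fair, but it does not remove the problem. The acute sentence has the same form, so if the late one covers radiation only, the acute one does too. CTCAE version 3.0 is then not assigned to Sutent toxicity at any time, even in the window for dose-limiting toxicity. Section 9.7 names no scale, and Sections 6 and 9.10 and Appendix 3 name no version. The early cutoff for radiation reactions in the variant schedule and the unmatched appendix reference remain on either reading.

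Several other objections stand and limit the point:
- The cells of the Appendix 3 tables say only grade. The hospitalization note speaks of events equivalent to a CTC grade, which leaves room for events recorded on another scale.
- Section 9.10 is limited to phase II, leaves much to the treating physician's judgment, and ends by referring to continued radiation. Whether it governs maintenance is itself unclear.
- For ejection fraction and severe hypertension, Section 9.7 acts on measured values and clinical findings, not on grade.
- Section 16 does not promise to pool events across the two periods. Separate tables would satisfy it, but drug toxicity would still be reported on two scales.

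One could also argue for a smaller remedy: a clause naming the scale for drug-related events after the acute window. That would close the main gap, but staff would have to settle the cause of an event before knowing how to grade it, and the variant's radiation reactions would still be classed as late after six days.

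**Conclusion.** The instructions on grading conflict and should be reconciled. Read literally, Section 12 places all maintenance Sutent toxicity, and in the variant schedule some concurrent-phase toxicity, on a late-radiation scale, against rules elsewhere that use CTC or CTCAE grades. Read narrowly, it leaves Sutent toxicity without a stated scale and version. On the literal reading, and under the assumptions above, about 80% of Sutent dosing days are affected at 6.4 months, within a range of about 47% to 88%, and 0% if chemotherapy continues to progression.

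A reader might infer more than the document supports:
- That maintenance toxicity never receives a CTC grade. Sections 6 and 9.10 themselves call for such grades, so the protocol contradicts itself and does not rule them out.
- That the toxicity of the regimen will be understated. The categories of the RTOG scale are not in the protocol, and no direction of bias can be derived from it.
- That 80% of grades are lost. The figure counts dosing days in one kind of patient, not events.
- That dose escalation or serious adverse event reporting to the supporting company is compromised by the switch. Neither is.

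This is a matter to correct in the text, not a threat to the phase I decision.

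**What to change.** In Section 12, state that adverse events of any cause are graded by CTCAE version 3.0 from the first Sutent dose through follow-up, and that the RTOG late scale is an additional grade for late radiation effects only. Reconcile this with Sections 6 and 9.10 and the hospitalization note in Appendix 3, so that all refer to the same scale and version. The severity summary in Section 16 can then rest on one scale. Supply the RTOG scale as an appendix or correct the reference.

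The cost is a sentence or two and matching fields on the case report form. The small downside is that late radiation effects are graded twice. No visits or tests are added, and no dose or clinical rule changes.

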**13. MEASUREMENT OF EFFECT**

- Response and progression will be evaluated in this study using the new international criteria proposed by the RECIST Committee. (38) Changes in only the largest diameter (unidimensional measurement) of the tumor lesions are used in the RECIST criteria.
- All lesions (except lesions seen on bone scan alone) are considered to be target lesions and are measurable. They are defined as being accurately measured in one dimension (longest diameter to be recorded). All tumors must be recorded in millimeters (or decimal fractions of centimeters) using a ruler or caliper.
- Lesions seen on bone scan only are not measurable and therefore are evaluated separately
- All baseline evaluation should be performed as closely as possible to beginning of the treatment and never more than 4 weeks before the beginning of treatment.
- The same method of assessment and the same technique should be used to characterize each identified and reported lesion at baseline and during follow-up.
- First assessment should be performed 4-6 weeks after completion of radiation therapy.
- Response Criteria for all lesions (except lesions seen only on bone scan):
  - Complete response (CR): Disappearance of all lesions
  - Partial response (PR): At least 30% decrease in the sum of the longest diameter (LD) of all lesions, taking as a reference the baseline sum LD
  - Progressive disease (PD): At least a 20% increase in the sum of the LD of the target lesions, taking as a reference the smallest sum LD recorded since the treatment started or the appearance of one or more new lesions
  - Stable disease (SD): Neither sufficient shrinkage to qualify for PR or sufficient increase to qualify for PD, taking as reference the smallest LD since the treatment started.
- Response Criteria for lesions seen only on bone scan:
  - Complete response (CR): Disappearance of lesion.
  - Stable disease (SD): Persistence of lesion on bone scan.
- Evaluation of best overall response:
  - The best overall response is the best response recorded from the start of the treatment until disease progression/recurrence (taking as reference for progressive disease the smallest measurements recorded since the treatment started). The patient’s best response assignment will depend on the achievement of both measurement and confirmation criteria:

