**ELIGIBILITY CHECK LIST**

The following questions will be asked at Study Registration:

______ Name of institutional person registering this case?

______ Has the eligibility checklist been completed?

______ Is the patient eligible for this study?

______ Date the study-specific Consent Form was signed? (must be prior to study entry)

______ Patient’s Initials (First Middle Last) [If no middle initial, use hyphen]

______ Verifying Physician

______ Patient’s ID Number

______ Date of Birth

______ Race

______ Ethnic Category (Hispanic or Latino; Not Hispanic or Latino; Unknown)

______ Gender

______ Patient’s Country of Residence

______ Zip Code (U.S. Residents)

______ Patient’s Insurance Status

______ Will any component of the patient’s care be given at a military or VA facility?

______ Treatment Start Date

______ Blood kept for cancer research?

______ Blood kept for medical research?

______ Allow contact for future research?

______ Is there a biopsy proven malignancy?

______ Was a PET/CT or CT/MRI chest/abdomen/pelvis AND bone scan performed?

______ Specify the date of CT, MRI, bone scan or PET/CT (mm-dd-yyyy)

______ Number of measurable lesions on the CT, MRI, bone scan or PET/CT?

______ Size of largest lesion?

______ Are all visible lesions treated within the radiation fields according to protocol criteria.?

______ If not, are these lesions being treated with an alternate modality (surgery, radiofrequency ablation, photodynamic therapy, focused ultrasound, intracranial radiosurgery, standard fractionation radiation therapy)

______ Age?

______ Zubrod Performance Status?

______ Results of ANC (cells/mm3)

______ Date of ANC (mm-dd-yyyy)

______ Results of platelet count (cells/mmз)

______ Date of platelet count (mm-dd-yyyy)

______ Results of hemoglobin (g/dl)

______ Date of Hemoglobin (mm-dd-yyyy)

______ Was an INR, total bilirubin, albumin, alkaline phosphatase, ALT and AST drawn within 2 weeks prior to study entry?

______ Date additional pretreatment labs were drawn? (mm-dd-yyyy)

______ Does the patient have any history of non-inducible bleeding? (12/16/09)

______ If the patient is on any blood thinner (Coumadin, lovenox, aspirin, plavix, NSAIDs, etc) can this be discontinued prior to starting protocol therapy? (12/16/09)

______ Was Chest CT or PET/CT performed within 30 days of study entry?

______ Was a negative serum pregnancy test obtained within 72 hours prior to registration?

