**Table 3**

| **All Measurable Lesions** | **Lesions on bone scan only** | **New Lesions** | **Overall Response** |
| --- | --- | --- | --- |
| CR | CR | No | CR |
| CR | SD | No | PR |
| PR | SD | No | PR |
| SD | Any | No | SD |
| PD | Any | Yes or No | PD |
| Any | Any | Yes | PD |

CR = complete response; PD = progressive disease; PR = partial response; SD = stable disease

- Note:
  - Patients with a global deterioration of health status requiring discontinuation of treatment without objective evidence of disease progression at that time should be classified as having “symptomatic deterioration.” Every effort should be made to document the objective progression, even after discontinuation of treatment.
  - In some circumstances, it may be difficult to distinguish residual disease from normal tissue. When the evaluation of complete response depends on this determination, it is recommended that the residual lesion be investigated (fine needle aspirate/biopsy) before confirming the complete response status.
- Confirmatory Measurement/Duration of Response
  - Confirmation
    - To be assigned a status of PR or CR, changes in tumor measurements must be confirmed by repeat assessments that should be performed at least 16 weeks after the criteria for response are first met.
  - Duration of Overall Response
    - The duration of overall response is measured from the time measurement criteria are met for CR or PR (whichever is first recorded) until the first date that recurrent or progressive disease is objectively documented (taking as reference for progressive disease the smallest measurements recorded since the treatment started).
    - The duration of overall CR is measured from the time measurement criteria are first met for CR until the first date that recurrent disease is objectively documented
  - Duration of Stable Disease
    - Stable disease is measured from the start of the treatment until the criteria for progression are met, taking as reference the smallest measurements recorded since the treatment started.
- Progression-Free and Overall Survival
  - Progression-free (time to progression): From the date of registration to the date of progressive disease or death
  - Overall survival time: From the date of registration to the date of death or date of last patient contact if censored

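### Lesions treated by non-protocol surgery, ablation or radiation stay in the response sum, so removing one that makes up 30% or more of it scores as a response

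*Protocol*

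**What the plan says.** Scoring rules (protocol, Section 13):

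- Target lesions: "All lesions (except lesions seen on bone scan alone) are considered to be target lesions and are measurable".
- "Complete response (CR): Disappearance of all lesions". PR is a fall of at least 30% from baseline in the summed longest diameters of all lesions. Progressive disease (PD) is a rise of at least 20% from the smallest sum, or any new lesion. The cause of a change is not part of any rule.
- PFS runs "From the date of registration to the date of progressive disease or death".
- Baseline imaging is to be as close as possible to the start of treatment, with a limit of 4 weeks. CR and PR need confirmation at 16 weeks or later.

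Non-protocol local treatment:

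- For visible lesions not treated in the protocol fields, the eligibility checklist asks: "are these lesions being treated with an alternate modality (surgery, radiofrequency ablation, photodynamic therapy, focused ultrasound, intracranial radiosurgery, standard fractionation radiation therapy".
- Section 11.1 says that chemotherapy, surgery or radiation may be given for clinical need, and that "they may be performed two weeks before or after days 1-28 of protocol therapy". In its worked example such treatments "are allowed by protocol but are not considered" on-protocol therapy. The one stated consequence is that their toxicity is recorded but is not dose-limiting.
- Section 11.2: "If patients have documented progression during additional chemotherapy and/or maintenance Sutent, the patient will be taken off protocol". The intervention itself does not take a patient off protocol.

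PFS is a phase II primary endpoint and response rate is secondary (Section 1).

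**The concern.** The protocol separates non-protocol local therapy from the regimen when it counts toxicity, but not when it scores efficacy. A lesion can be in the baseline sum, be removed by a surgeon or by ablation, and then count as zero at follow-up. Its disappearance is credited to radiation plus Sutent. The phase II part has no control arm in which the same inflation would occur, so any such response biases the response rate towards the regimen.

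A second consequence concerns PFS and depends on how Section 11.1 is read. If surgery or radiation is allowed after treatment without progression, a lesion that is growing, but not enough to raise the whole sum by 20%, can be treated before it produces a patient-level event.

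**Working it through.** **The plan's own figures.** A 25% gain on 6.4 months is 1.6 months. With SD 3.2 and 38 patients the standard error is 3.2/√38 = 0.519, and a two-sided one-sample test has power Φ(1.6/0.519 - 1.96) = 0.869, against 87% stated. For 2-year PFS, taking 5% against 15%, a rule of at least 5 of 38 has exact α = 0.040 and power 0.693, against 70% stated. Both figures reproduce and neither is disputed. The question is how endpoints are scored.

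**Response.** If a lesion makes up a share s of the baseline sum and is removed while the others stay unchanged, the sum changes by -s. PR needs s ≥ 30%. For k equal measurable lesions, s = 1/k; eligibility allows 1 to 5 sites.

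| Equal lesions | Change on removing one | Score |
| --- | --- | --- |
| 1 | -100% | CR |
| 2 (60 to 30 mm) | -50% | PR |
| 3 (90 to 60 mm) | -33% | PR |
| 4 | -25% | stable disease |
| 5 | -20% | stable disease |

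- With four or five equal lesions, two removals are needed (-50%, -40%).
- One dominant lesion is enough: for 6, 2, 2, 2 and 2 cm, removing the largest gives -6/14 = -43%. For 3, 2, 2, 2 and 2 cm it gives -3/11 = -27%, which is not a PR.
- A persisting bone-scan-only lesion does not block the response. Table 3 in Section 13 turns CR with a stable bone lesion into PR, and leaves PR as PR.
- The 16-week confirmation does not help, because a resected lesion stays absent.

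**When this can happen.** A procedure done before the baseline scan does no harm, because the lesion never enters the sum. One done after it does. Three routes are open on the text: a lesion left to another modality under the checklist, for which no timing relative to baseline is given; surgery two weeks before day 1 following a scan up to 4 weeks before treatment; and treatment after day 28.

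**PFS.** With k equal lesions, the sum reaches the PD threshold only when one lesion alone has grown by 20% × k: 40% for two lesions, 60% for three, 100% for five. Take two 30 mm lesions, one of which grows to 41 mm. The sum is 71 mm, and (71 - 60)/60 = +18%, so this is not PD. If that lesion is then resected, the sum is 30 mm, which is -50% from baseline. The patient is scored PR and has had no PFS event.

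**Size of the PFS effect.** The documents give no rate of such interventions, so it cannot be estimated. To show sensitivity only: if the true 2-year rate were 5% and local therapy kept a further 2, 5 or 8 percentage points of patients progression-free (assumed values), the false-positive rate of the 5-of-38 rule would go from 0.040 to 0.12, 0.33 or 0.56.

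**The case against.** Several points on the other side are sound.

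- A reader might infer that local failures go unrecorded. They do not. Section 16 has every individual lesion scored CR, PR, SD or PD, and local and distant failures summarised. A lesion growing from 30 to 41 mm (+37%) would be recorded as progressing if it is imaged. Those records do not, however, feed the PFS or patient-level response definitions.
- A reader might infer that removing any lesion scores as a response. It does so only from 30% of the sum upwards.
- A reader might infer that a true PFS event is always lost. Growth below 20% of the sum is not PD with or without surgery, and new lesions remain PD. Removal also lowers the reference sum: in the example PD is then reached at 36 mm, after 6 mm of growth, against 12 mm on the original 60 mm sum.
- Section 11.1 is headed as covering interventions before protocol therapy. Its example gives only chemotherapy afterwards, the schemas show only chemotherapy and then Sutent, and Section 11.2 allows any intervention once progression is documented. All this favours the narrow reading. The operative sentence nonetheless covers both sides of days 1-28 and names surgery and radiation. The PFS consequence depends on that sentence; the response consequence does not.
- The baseline should be as close to treatment as possible, and the worked example re-images after surgery. Using a scan from before the resection goes against the intent, but the 4-week limit permits it.
- Appendix 3 has an independent investigator confirm the measurements and source documents of every PR and CR. That puts the case before a second reader but gives no rule for scoring it.
- All involved sites are meant to be irradiated, so other modalities should be the exception. Censoring rules for PFS may also sit in an analysis plan that is not shown. The all-lesions target rule, by contrast, is fixed in the protocol itself.

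**Conclusion.** The point stands for response. Followed as written, Section 13 scores PR or CR when a non-protocol procedure removes a sole lesion, one of two or three equal lesions, or a dominant lesion making up at least 30% of the sum, and no other section prevents it. The bias favours the regimen and falls on a secondary endpoint. One removal among four or five equal lesions stays stable disease. The arithmetic assumes that the lesion was in the baseline sum and that the other lesions are unchanged.

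For PFS the point is conditional. If Section 11.1 allows local treatment after day 28 without progression, growth below the sum threshold can be treated without a patient-level event. The size is unknown, and the documents do not support a claim that the primary endpoint is biased by any particular amount.

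**What to change.** 1. In Section 13, exclude any lesion treated by a non-protocol local modality from both the baseline and the follow-up sums and from the CR/PR determination. PD documented before the procedure stands. In the two-lesion example the evaluable sum is then 30 mm before and after, a change of 0%, and the patient is scored on the irradiated lesion alone.
2. Take the baseline measurement after any local procedure performed before day 1.
3. Record the date and site of each non-protocol local treatment. Report PFS sensitivity analyses for such treatment given before documented PD: once counted as an event on that date, and once censored at that date. Leave the primary PFS event as it is. Counting every such treatment as progression would fail a patient whose stable or shrinking residual lesion is resected, and a new lesion is already PD.
4. Reconcile the heading of Section 11.1 with its text. This point takes no position on which interventions should be allowed.

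The cost is some wording in Section 13 and a date field. The reported response rate may be slightly lower, and some patients will have fewer evaluable lesions. A patient left with no measurable lesion can go in the not-assessable category that Section 16 already has and counts as non-response.
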